## Abstract

Smoking cessation after myocardial infarction (MI) is critical, yet many patients relapse soon after discharge, especially where structured follow-up is limited. Telegram provides a low-cost tool for implementing chatbot-based behavioral support that hospitals can run with minimal technical resources. The aim is to conduct TELEGRAM-MI trial tests to ascertain whether a 6 month Telegram-based chatbot improves cessation outcomes compared with routine discharge advice provided by cardiology staff. This pragmatic, single-blind, randomized trial, starting in 2026 at a regional clinical hospital in Russia, will enroll adult current cigarette smokers hospitalized with acute MI who use Telegram. Participants are randomized 1 : 1 to routine discharge advice plus a passive bot (control) or to the same advice plus an active 6 month behavioral support bot. The intervention includes motivational messages, craving-management tools, an SOS function, weekly check-ins, and relapse-prevention sequences. The primary outcome is 30 day point prevalence abstinence at 6 months, verified by a blinded assessor and a relative. Secondary outcomes include 7 day abstinence at 1 and 3 months, changes in cigarettes/day, nicotine dependence, motivation, engagement, and time to relapse. Analysis will follow intention-to-treat principles. Recruitment begins in January 2026. Results are expected after completion of the 6 month follow-up in October 2026. The intervention could enhance cessation, sustain recovery after MI, and offer a practical way to extend secondary prevention beyond the hospital site.

## Introduction

Tobacco smoking remains a major global health problem, and helping people quit is difficult even in settings with established cessation programs^1,2^. For patients who survive a myocardial infarction (MI), the cardiac event often becomes a strong trigger to stop smoking, but maintaining abstinence after discharge remains challenging^3^. In Russia, usual care typically consists of brief physician advice at discharge, with almost no structured long-term follow-up. As a result, many patients relapse shortly after returning home, despite the high risk of recurrent cardiac events^4^. At the same time, messaging platforms such as Telegram are used daily by millions of people and can deliver ongoing behavioral support at very low cost^5^. Most hospitals do not have established digital follow-up systems. Still, automated chatbots offer a practical way to extend clinical care beyond the hospital site, and help patients stay motivated during recovery^6^. Because Telegram allows rapid deployment of automated support tools without collecting sensitive personal data, it represents a promising channel for scalable digital health interventions^7^. Based on this opportunity, we designed the TELEGRAM-MI trial to test whether a ^,^6-month^6,8^ Telegram-based support program can improve smoking cessation outcomes in MI survivors compared with usual care only.

## Methods

### Study design

The TELEGRAM-MI trial is a pragmatic, randomized controlled trial with blinded outcome assessment, initially conducted as a single-center study with a protocol structure that allows for potential multicenter expansion. Participants will be randomized in a 1 : 1 ratio to the intervention or control group. The trial will be conducted in inpatient cardiology departments at the Ulyanovsk Regional Clinical Hospital. The pragmatic design aims to assess the intervention’s effectiveness in real-world clinical practice. The protocol was approved by the Local Ethics Committee of the clinical center (Ulyanovsk regional hospital, #PN0104122025, 04.12.2025) and registered on ClinicalTrials.gov (NCT07230249). Written informed consent will be obtained from all participants.

### Eligibility criteria

Participants will be identified, screened, and enrolled during hospitalization for acute MI.

### Inclusion criteria

The inclusion criteria will be: 1) adults aged ≥18 years; 2) a confirmed diagnosis of acute MI and being current cigarette smokers (≥1 cigarette/day in the month before hospitalization – only cigarette smoking will be considered to ensure a homogeneous study population); 3) regular user of Telegram on a personal smartphone; 4) fluent in Russian; and 5) willing to provide written informed consent and contact details of a close relative/cohabitant for outcome verification.

### Exclusion criteria

Exclusion criteria will be: 1) potential smoking cessation >1 month before MI; 2) severe physical or cognitive impairment preventing smartphone use; 3) severe, uncontrolled mental illness impeding protocol adherence; 4) severe comorbid condition with a poor short-term prognosis; and e) unwillingness to provide a relative’s contact for verification.

### Recruitment, consent, and randomization

A treating cardiologist or study nurse will screen potential participants. After providing written informed consent, participants will be assisted in connecting to the study’s Telegram bot before discharge. Randomization will occur automatically within the bot upon completion of the baseline assessment. The allocation sequence (1 : 1) will be computer-generated with variable block sizes by an independent statistician using R software and integrated into the bot’s backend. Allocation concealment is ensured, as the enrolling clinician will have no access to the sequence; the group assignment is revealed only by the bot after the baseline survey is finalized. The flow of participants through the study is illustrated in Figure 1.

**Figure 1 F1:**
[figure not shown]
Participant flow diagram of the TELEGRAM-MI pragmatic, single-blind, randomized trail conducted in a regional clinical hospital in Russia (2026)

### Blinding

While participants cannot be fully blinded to the intervention, they are not explicitly informed of their group assignment. As well, outcome assessment is blinded (single-blind). The assessor conducting the 6 month telephone verification will be unaware of group allocation and will have no access to bot interaction data.

### Interventions

#### Control group (usual care + passive bot)

Participants receive usual care (advice to quit and pharmacotherapy at the discretion of the physician) and are connected to a Telegram bot used only for completing baseline and follow-up assessments (1, 3, and 6 months). The control bot sends no smoking-cessation advice, motivational content, or personalized feedback.

#### Intervention group (usual care + active telegram support)

Participants received a 6 month behavioral intervention via a Telegram chatbot. The bot delivered content across several categories (e.g. motivational^9^, behavioral coping strategies^10^, check-in prompts) following a tapered frequency schedule: daily messages during months 1–2, reducing to three times per week in months 3–4, and weekly in months 5–6. Personalization was rule-based: initial intensity was informed by the baseline Fagerström score, and subsequent support was dynamically adapted based on weekly check-in responses (e.g. increased outreach following reports of high cravings or lapse). Bot script will be shared.

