### Outcomes and assessments

#### Primary outcome

The primary outcome will be 30 day point prevalence abstinence (PPA) at 6 months, defined as self-reported non-smoking via bot for the preceding 30 days corroborated by a relative/cohabitant report during a blinded telephone interview. Participants with missing data or data not corroborated by a relative after two attempts will be considered smoking.

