#### Secondary outcomes

Secondary outcomes will include: 7 day point prevalence abstinence (via bot) at 1 and 3 months; change in cigarettes per day; change in Fagerström test for nicotine dependence (FTND) score; change in Prochaska’s Motivation to Quit Smoking Questionnaire score (0–8); engagement metrics (weekly check-in completion rate, SOS-button presses); intervention acceptability/satisfaction score (12-item Likert scale); and time to first relapse (any cigarette) after ≥24 h of abstinence. Data collection, time points, mode of assessment, and the questionnaires administered are summarized in Table 1. Missing data will be reported and accounted for in the analysis (for secondary outcomes based on available cases).

**Table 1 T1:** Schedule of outcomes and assessments in the TELEGRAM-MI pragmatic randomized trial testing a Telegram-based intervention for smoking cessation after myocardial infarction, Russia, 2026

Outcome	Type	Measurement tool/ source	Baseline	1 **month**	3 **months**	6 **months**
30 day point prevalence abstinence	Primary	Blinded phone interview + relative confirmation				X
7 day point prevalence abstinence	Secondary	Telegram bot self-report		X	X	X
Cigarettes per day	Secondary	Telegram bot self-report	X	X	X	X
FTND score	Secondary	Fagerström test for nicotine dependence (bot)	X			X
Motivation to quit^a^	Secondary	Self-rated scale via Telegram bot	X			X
Engagement metrics^b^	Secondary	Automatically logged by Telegram bot		X	X	X
Acceptability/ satisfaction score	Secondary	Custom questionnaire via Telegram bot (intervention only)				X
Time to first relapse	Secondary	Continuous monitoring via weekly check-ins (bot)		X	X	X

a Prochaska questionnaire (0–6).

b Check-ins, openings etc.

FTND: Fagerström test for nicotine dependence.

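### The bot that delivers the treatment is also the only stated route for the secondary outcomes, so an active-arm participant who blocks it to stop the messages is lost to those assessments

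*Protocol article*

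**What the plan says.** **Treatment.** The Intervention group section states: "Participants received a 6 month behavioral intervention via a Telegram chatbot". The schedule is "daily messages during months 1–2, reducing to three times per week in months 3–4, and weekly in months 5–6". Support adapts to weekly check-ins, for example "increased outreach following reports of high cravings or lapse".

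**Control.** Under Control group, participants are "connected to a Telegram bot used only for completing baseline and follow-up assessments (1, 3, and 6 months". The section adds: "The control bot sends no smoking-cessation advice, motivational content, or personalized feedback".

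**Measurement.** Secondary outcomes lists "7 day point prevalence abstinence (via bot) at 1 and 3 months". Table 1 gives the bot as the source in every secondary row, including cigarettes per day, FTND, motivation and time to first relapse (from weekly check-ins). It names no other route for any of them. The Secondary outcomes section bases their analysis on available cases.

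**Primary outcome.** The Primary outcome section takes the participant's own report through the bot and the relative's report by telephone. It adds: "Participants with missing data or data not corroborated by a relative after two attempts will be considered smoking". Table 1 instead gives a telephone interview by a blinded assessor plus the relative's confirmation, and does not name the bot.

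**The concern.** Stopping a treatment and leaving follow-up should be separable. Here both run through the bot in the active arm, and the article describes no way to stop one and keep the other. The reason to leave is also unequal. Active participants get frequent messages, and more of them after reporting a lapse, while controls are described as getting only surveys.

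If people who have lapsed are the ones who block the bot, the available cases in the active arm are enriched for abstainers and the intervention looks better than it is. If confident quitters leave because they no longer want the messages, the bias runs the other way. For time to relapse, a participant who blocks the bot after an unreported lapse would be censored as relapse-free at that point. An analysis plan cannot recover outcomes that were never collected, so the remedy lies in the measurement route.

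**Working it through.** **1. The plan's own sample size.** Inputs from Sample size calculation: 10% versus 30%, 80% power, two-sided alpha 0.05, 15% dropout. The arcsine formula gives 60 per group, the unpooled formula 59 and the pooled formula 62. The stated 60 is reproduced. Inflation: 60/0.85 = 70.6, rounded up to 71 per group, 142 in total, as stated. The point does not rest on a sample-size error. The 15% is not split by arm.

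**2. Scheduled contact.** Take 61 days per two months and one message per scheduled day (assumptions). Active arm: 61 + 61/7 × 3 ≈ 26 + 61/7 ≈ 9, in total about 96 message days. Control arm, as its section describes it: 3 follow-up assessments.

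**3. Available-case bias in 7 day abstinence.** All leaving rates are assumptions. Let true abstinence be p = 30% in both arms, so there is no effect. Controls lose 10% unrelated to smoking, which leaves 71 × 0.9 = 63.9 observed at 30%. In the active arm a share x of smokers and y of abstainers leave. Then

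observed active rate = p(1 − y) / [p(1 − y) + (1 − p)(1 − x)].

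Worked example, x = 40%, y = 10%: 0.27 / (0.27 + 0.42) = 39.1%.

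| Smokers leaving x | Abstainers leaving y | Active arm lost overall | Observed active rate | Bias (points) | Two-sided false-positive risk |
|---|---|---|---|---|---|
| 20% | 10% | 17% | 32.5% | +2.5 | 6.1% |
| 30% | 10% | 24% | 35.5% | +5.5 | 9.8% |
| 40% | 10% | 31% | 39.1% | +9.1 | 17.5% |
| 30% | 30% | 30% | 30.0% | 0 | 5.0% |
| 10% | 20% | 13% | 27.6% | −2.4 | 6.0% |
| 10% | 30% | 16% | 25.0% | −5.0 | 9.4% |

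The last column uses the normal approximation for two proportions with the observed numbers. The fourth row shows that heavy loss alone does not bias the rate; loss related to smoking does.

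**4. Primary outcome, only if self-report must come through the bot.** Suppose a share d of active-arm abstainers leave and are scored as smokers, with no such loss in controls. The observed active rate is 0.30 × (1 − d). Power is by exact enumeration of the chi-squared test without continuity correction, 71 per group.

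| Case | Active vs control | Power |
|---|---|---|
| No loss | 30% vs 10% | 86.8% |
| d = 10% | 27% vs 10% | 76.2% |
| d = 20% | 24% vs 10% | 61.7% |
| d = 30% | 21% vs 10% | 44.6% |
| 15% lost in both arms | 25.5% vs 8.5% | 79.2% |
| 15% lost in the active arm only | 25.5% vs 10% | 69.4% |

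Since the plan already allows for 15% dropout, the fair comparator is 79.2%, not 86.8%. At the same 15%, one-sided loss costs about 10 points of power. Under Table 1's telephone interview, blocking the bot does not by itself cause this loss.

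**The case against.** **The article is condensed.** Opt-out commands or a back-up contact route may be in the full protocol or the bot script. This stands as a caution: the point can say only that the bot is the sole stated route. But the article does commit to that route in Table 1 and to available cases, so the point rests on what is written and not on silence alone.

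**Leaving is inferred.** No figure in the article shows that message load drives people away, and the direction of any bias is not determined. Muting the chat is not blocking it: a muted survey can still be answered. All of this stands.

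**Control loss need not be zero.** Controls offered no support may also stop answering. Table 1 takes time to relapse from weekly check-ins without restricting them to one arm, in conflict with the Control group section. If controls do get weekly prompts, the load is less unequal, though they still receive no support messages.

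**Mixed models soften the loss.** They use all observed waves, which helps cigarettes per day (baseline and three follow-ups). They help less for FTND and motivation, which Table 1 schedules only at baseline and 6 months, and they are planned for continuous outcomes, not for 7 day abstinence.

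**A tempting stronger reading** is that the design prevents an intention-to-treat estimate of the primary outcome and cuts its power from 87% to as low as 45%. The documents do not support that. It needs the bot-only wording of the Primary outcome section, which Table 1 contradicts, together with assumed heavy loss in one arm and none in the other. Scoring missing as smoking is also prespecified and, for loss in the active arm alone, conservative.

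**Conclusion.** The point holds as a design weakness in the secondary outcomes. Treatment and measurement share the bot in the active arm, no other route is stated, and the support messages go to that arm only. Missing data may therefore differ by arm and relate to smoking. The size is unknown. Over the assumed rates the bias in 7 day abstinence runs from about −5 to +9 points, with false-positive risk up to about 17.5%, and it is zero if leaving is unrelated to smoking.

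For the primary outcome the exposure is conditional on which of the two conflicting descriptions applies. A reader should not infer that such bias has been shown, that it favours one arm, or that losses will occur in the active arm only. The change is worth making because it is cheap and should come before data accrue.

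**What to change.** 1. In both arms, send the 1-, 3- and 6-month surveys from a common assessment chat separate from the support chat, so that blocking the support chat leaves the assessments in place. Alternatively, give the active bot a mode that stops support messages and keeps surveys, reusing the control bot.
2. Log the date of any switch, analyse participants in their randomised arm, and report missingness by arm at each time point.
3. Reconcile the Primary outcome section with Table 1 on whether the participant's 6 month report comes through the bot or by telephone.

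**Cost:** a small bot change and a few protocol sentences; no change to sample size. An easy opt-out may slightly reduce exposure to the intervention; the separate-chat version largely avoids this.

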### Outcomes and assessments

#### Primary outcome

The primary outcome will be 30 day point prevalence abstinence (PPA) at 6 months, defined as self-reported non-smoking via bot for the preceding 30 days corroborated by a relative/cohabitant report during a blinded telephone interview. Participants with missing data or data not corroborated by a relative after two attempts will be considered smoking.

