### Sample size calculation

Assuming 6 month abstinence rates of 10% (control)^4^ and 30% (intervention), 120 participants (60/group) are needed for 80% power with a two-sided alpha of 0.05. Allowing for a 15% dropout rate, the target sample size is 142 (71/group). The assumptions are based on prior evidence, where abstinence after brief advice is around 10%^9^, and a larger effect is considered plausible due to the acute motivational impact of myocardial infarction^11^.

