### Statistical analysis

Analyses will follow the intention-to-treat principle, with participants lost to follow-up considered smokers for the primary outcome. Baseline characteristics will be presented descriptively in Table 2^6^. The primary analysis will compare 6 month abstinence rates using a chi-squared test, reporting absolute risk difference and relative risk (RR) with 95% confidence intervals (CIs). Continuous outcomes will be analyzed using linear mixed models. Time to first relapse will be analyzed with Kaplan-Meier curves and Cox regression. Exploratory analyses will use logistic regression to assess associations between baseline factors, engagement, and cessation. A per-protocol secondary analysis will include intervention-group participants who completed ≥60% of weekly check-ins during the first 3 months and had their final assessment within 6 months±3 weeks; this criterion does not apply to the control group.

**Table 2 T2:** Baseline demographic and clinical characteristics of TELEGRAM-MI participants by trial arm (template for future Table)

Characteristics	Total	Intervention	Control

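### The primary endpoint scores a relative not reached in two attempts the same as one who contradicts the participant, so non-contact can turn true quitters into smokers

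*Protocol article*

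**What the plan says.** Under Primary outcome, abstinence needs two things: a report through the bot of no smoking for 30 days, and that report being "corroborated by a relative/cohabitant report during a blinded telephone interview". The next sentence fixes the default: "Participants with missing data or data not corroborated by a relative after two attempts will be considered smoking". The article does not define an attempt further; a contact attempt is the natural reading.

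Under Inclusion criteria, participants must supply "contact details of a close relative/cohabitant for outcome verification". No second contact is described.

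Under Statistical analysis, the intention-to-treat rule is repeated, "with participants lost to follow-up considered smokers for the primary outcome", and the test is named: "The primary analysis will compare 6 month abstinence rates using a chi-squared test", with the absolute risk difference and the relative risk both reported. Under Blinding, the assessor who makes the six-month call "will be unaware of group allocation and will have no access to bot interaction data".

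Strengths and limitations presents relative verification as protection against detection bias and acknowledges over-reporting. It does not mention error in the other direction.

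**The concern.** A relative who contradicts the participant is evidence about smoking. A relative who does not pick up the phone is not. The endpoint merges the two, and it does so after only two attempts to what may be a single third party. For a participant who has truly stopped, the result then depends on whether someone else answers.

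The error is proportional to abstinence. If the same share of true abstainers is lost in each arm, both observed rates and their difference shrink by that share, and power falls. If the two reasons for non-corroboration are not recorded separately, nobody can later tell low quit rates from unanswered calls, or check whether non-contact differed by arm.

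**Working it through.** **Inputs from the article.** 10% (control) and 30% (intervention) abstinent at six months, two-sided alpha 0.05, 80% power, 60 per group, 15% dropout, 71 per group. Per-call reach is not given, so it is assumed below.

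**The plan's own figure.** The unpooled normal formula gives (1.960 + 0.842)² × (0.1×0.9 + 0.3×0.7) / 0.2² = 58.9 per group. The arcsine formula gives 59.01, so 60. The pooled formula gives 62. Power at 60 per group (pooled) is 78.9%. Inflation: 120/0.85 = 141.2, so 142, or 71 per group. The stated sample size reproduces.

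**Model of the rule.** With per-call reach c and k independent calls, reach R = 1 − (1 − c)^k. Observed rates are 0.10R and 0.30R, so the risk difference is 0.20R and the relative risk stays 0.30R/0.10R = 3.0. Every randomised participant stays in the denominator, so n = 71 per group. Power = Φ[(d − 1.96·se0)/se1], where se0 uses the pooled rate and se1 the separate rates.

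**One case in full.** With c = 0.5 and k = 2, R = 1 − 0.5² = 0.75 and the rates are 7.5% and 22.5%, so d = 0.15.
- se0 = √(0.15×0.85×2/71) = 0.0599
- se1 = √[(0.075×0.925 + 0.225×0.775)/71] = 0.0586
- (0.15 − 1.96×0.0599)/0.0586 = 0.555, so power is 71.1%

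**Range, no dropout.**

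| Assumed reach per call | Reached in two | Risk difference (points), power | Six calls: risk difference (points), power |
|---|---|---|---|
| 40% | 64% | 12.8, 62.9% | 19.1, 83.2% |
| 50% | 75% | 15.0, 71.1% | 19.7, 84.7% |
| 70% | 91% | 18.2, 80.9% | 20.0, 85.3% |
| 80% | 96% | 19.2, 83.5% | 20.0, 85.4% |
| 90% | 99% | 19.8, 84.9% | 20.0, 85.4% |
| all reached | 100% | 20.0, 85.4% | – |

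Power drops below 80% once about 11% of abstainers' relatives are missed. With two independent calls that means reach per call below 1 − √0.107, about 67%.

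**With the planned dropout.** If 15% of abstainers in each arm are also lost and scored as smoking, the rates before any non-contact are 8.5% and 25.5%, and power is 77.5%. Two attempts then give 62.7%, 72.7% and 75.4% at 50%, 70% and 80% reach per call.

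**Calls that are not independent.** Some relatives will be hard to reach on every call. If reach per call varies uniformly between relatives from 0 to 1 (mean 50%), R = 1 − 1/(k + 1). Six calls then reach 6/7 = 86%, not 98%, and power without dropout is 78%, not 85%.

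**Unequal non-contact.** If 10% of control and 20% of intervention abstainers are missed, the rates are 9% and 24%: risk difference 15 points, relative risk 2.67. With the shares reversed, they are 8% and 27%: 19 points and 3.38.

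**The case against.** The rule is pre-specified and conservative. There is no biochemical test, corroboration is part of the endpoint, and counting missing as smoking is a common convention. Where a participant falsely reports abstinence and the relative is not reached, scoring smoking is correct; the figures above leave that benefit out. Because the contact is a close relative or cohabitant whose details are an entry condition, reach may be high. At 80% to 90% per call, the loss is only about 0.5 to 2 points of power. All of this stands. It limits the size of the point but does not remove it, since the plan still scores non-contact and contradiction alike.

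Four stronger readings are tempting and are not supported:
- **That two attempts fall short of the plan's own six-week window.** The phrase "had their final assessment within 6 months±3 weeks" belongs to the per-protocol criterion, which is stated not to apply to controls. The article gives no trial-wide window for verification.
- **That the comparison is biased.** With equal non-contact the relative risk is unchanged and the risk difference moves towards zero. Unequal non-contact is neither shown nor ruled out, and the assessor is blinded.
- **That more calls would bring power back to about 85%.** That figure ignores the dropout already scored as smoking and treats calls as independent.
- **That a sensitivity analysis is missing.** It may be in an analysis plan that is not shown. The point rests on the endpoint definition alone.

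**Conclusion.** The concern holds in a limited form. As written, the endpoint can misclassify true abstainers because a relative was not reached, and it does not distinguish this from contradiction. The absolute quit rates, the risk difference and power fall; the relative risk does not, if non-contact is equal across arms. Under the assumptions above, and without dropout, two attempts cost between about 2 points of power (80% reach per call) and 14 points (50%). With 15% dropout scored as smoking, they cost about 2 to 15 points from a ceiling of 77.5%.

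These sizes rest on assumed contact rates, independent calls, and the reading that 10% and 30% are rates before any loss to non-contact. The change is worth making before outcome calls begin, because it is cheap and because the reason for non-corroboration may not be recoverable later if it was not recorded.

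**What to change.** 1. In the Primary outcome definition, replace two attempts with several, for example about six, on different days and at different times, made by the same blinded assessor. Six is a working suggestion, not a figure from the documents.
2. State a verification window that applies equally to both arms.
3. Ask the relative about the same 30 calendar days that the participant's report covers.
4. Take an optional second relative or cohabitant contact at consent.
5. Record contradicted and not reached as separate codes, and report both counts by arm.
6. Keep not reached as smoking in the primary analysis. Use self-report unless contradicted as a supporting analysis, noting that it is open to over-reporting.

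The cost is a few extra calls for relatives not reached early, one optional contact field, one extra status code and one supporting analysis. Randomisation, blinding, the primary test and the sample size stay as they are. The downside is a somewhat longer gap between self-report and corroboration, which step 3 is meant to contain. Further attempts will recover less than the independent-call figures suggest if some relatives are persistently unreachable.
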